# Peer2Me – evaluation of a peer supported program for adolescent and young adult (AYA) cancer patients: study protocol of a randomised trial using a comprehensive cohort design

**DOI:** 10.1186/s12885-024-12547-5

**Published:** 2024-07-02

**Keywords:** AYA, Cancer, Peer support, Mentoring, Emotional support, Young adults, Psychooncology

## Abstract

**Background:**

Developing cancer in young adulthood is a non-normative life event and associated with adverse physical, social and psychological consequences. High psychological distress is common in AYA cancer patients including anxiety, depression or fear of recurrence. At the same time, it is well known that AYA often report unmet needs for support, particularly in terms of informational exchange and emotional support from peers in order to benefit from shared experiences and enhance self-efficacy. Especially in the AYA group, interactions with other same-aged cancer patients may represent an essential resource in terms of coping with the disease, as family members and friends are often overwhelmed and struggling with helplessness. Currently, there is a lack of professional support services using peer support (e.g. psycho-oncological support, aftercare consultations, social legal counselling) or evaluated peer support interventions in Germany. Our aim is to assess the effectiveness of the Peer2Me intervention for AYAs, in which acute patients (mentees) are accompanied by an AYA survivor (mentor) over a period of three months.

**Methods:**

A prospective Comprehensive Cohort Design with repeated measures will be used to evaluate the effectiveness of Peer2Me for AYA. A sample of 180 patients in active cancer treatment aged 18 to 39 years will be enrolled and randomized to the intervention or control condition (a single AYA-specific consultation). Following mentor training, mentees and mentors are matched by diagnosis, age, and gender. The primary outcome is self-efficacy; secondary outcomes include measures of anxiety, depression, health literacy, life satisfaction and social support life. Outcomes will be measured at baseline before the intervention (t1), immediately after completion of the three-month intervention (t2) and three months after completion the intervention (t3). For the final analyses, we will use an intention-to-treat approach (ITT) and compare patients in the assigned treatment groups.

**Discussion:**

Peer2Me might be an important addition to existing professional psychosocial support services for young cancer patients. At the end of the study, a psycho-oncological intervention for young cancer patients undergoing acute treatment should be available, from which both mentors and mentees could benefit. The long-term continuity of Peer2Me should be ensured through collaboration with different partners.

**Trial Registration:**

The study was retrospectively registered on February 4, 2022 at clinicaltrials.gov (NCT05336318).

## Introduction

Cancer is a critical life event that can have a negative impact on quality of life, regardless of age. A cancer diagnosis during young adulthood presents individuals with unique challenges that must be navigated alongside typical developmental tasks, such as completing education or starting a family [1]. Stress induced by the disease and its treatment, including side effects, prolonged hospital stays resulting in social isolation, financial losses due to altered professional activities, or the loss of independence, can lead to significant psychological and social consequences, such as feelings of helplessness, anxiety, depression or familial conflicts [2].

AYAs are characterized by heightened vulnerability, particularly in terms of emotional distress. Research on the mental well-being of young adults with cancer indicates that up to 32% experience heightened psychological distress, anxiety, depression, and post-traumatic stress disorders [3–5]. Recent scientific research [6] indicates that AYA survivors are 55% more likely to report moderate distress compared to middle-aged or older cancer patients. The prospective longitudinal study, ’AYA-LE’, which included a sample of *n* = 514 young adults, confirms that 17% of patients have depressive symptoms and 42% exhibit anxious symptoms that remain stable over time [7]. Extended survival time results in approximately 60% of AYA patients experiencing high levels of fear of recurrence [8, 9], leading to reduced quality of life, both in the short and long term.

Self-efficacy is of critical importance in the well-being and outcomes of young cancer patients as it influences their ability to manage symptoms, distress, and the challenges associated with cancer treatment [10, 11]. Studies have indicated that self-efficacy influences cancer-related fatigue, health-related quality of life, and psychological adjustment in cancer survivors [12–14].

The impact of low self-efficacy on adolescent and young adult (AYA) cancer patients can have significant implications for their well-being and outcomes. Research indicates that low self-efficacy in AYA cancer patients is associated with higher levels of distress and poorer quality of life [15].

AYA patients with lower self-efficacy may encounter difficulties in coping with their diagnosis and treatment, leading to increased psychological distress and reduced overall quality of life [16, 17]. Additionally, low self-efficacy may impede AYA cancer patients’ ability to engage in self-care practices, adhere to treatment regimens, reduce healthcare utilization, and effectively cope with the challenges of cancer survivorship [16, 18].

These various strains are also evident in the reported care needs of AYAs. Research findings indicate that more than half of AYA patients have unmet information needs [19]. AYAs express a desire for information on long-term effects of cancer and treatments, including late effects, as well as financial matters and health-promoting behaviors related to sexuality, nutrition, and drug use [20, 21].

Sender et al. [22] demonstrated that patients’ psychological and healthcare information needs are consistent over time. If support needs remain unmet or only partially fulfilled, it may exacerbate psychological distress. Individuals experiencing psychological distress may require higher levels of support, making it necessary to implement a comprehensive psychosocial care plan to support AYAs throughout their treatment and survivorship [22].

Psycho-educational interventions and multimedia, such as web-based care-plans, are highly suitable for AYA [23, 24]. AYA cancer survivors, who are aware of available psychosocial services, such as cancer counselling centers, clinical liaison service, survivorship consultations, or social legal counseling, demonstrated a heightened motivation to use them during post-treatment care. Survivors must receive comprehensive information about psychosocial care to ensure positive outcomes [25].

Holland and colleagues identified several barriers to accessing psychosocial care. These barriers include personal factors such as severe physical impairment and lack of motivation, as well as systemic deficiencies such as a shortage of available services or insufficient interdisciplinary networking [26]. However, it is evident that regular and repeated screening and assessment of psychosocial issues and needs are absent. There is also a lack of widespread, age-appropriate support and psychosocial care specifically tailored to the needs of young cancer patients [27, 28].

Several studies have shown that the desire for peer-led support is highly significant for young cancer patients, who can derive substantial benefits from such interactions [29, 30]. Interaction with peers on an eye-to-eye level can help maintain normality and cope with upcoming developmental tasks such as identity formation or the development of a positive self-image [31, 32].

Cancer patients often do not want to burden their family and friends with their illness and are reluctant to communicate their fears and worries in this context [33, 34]. Several studies have confirmed that young cancer patients want to interact with others of the same age in order to rely on peer experiences and benefit from positive coping styles [35–37]. Heisler [38] emphasizes that the effectiveness of peer support is based on the non-hierarchical and reciprocal relationship between participants and has developed a model that clearly illustrates the benefits (Fig. 1).

**Fig. 1 Fig1:**
[figure not shown]
Hypothesized effects of peer support on self-care attitudes, behaviors and outcomes. (adapted from Heisler [38])

The relationship between self-efficacy and peer support in young cancer patients is a significant factor in their coping mechanisms and overall well-being. Peer support has been found to play a critical role in how adolescents and young adults with cancer manage their diagnosis and treatment decisions, influencing their ability to cope effectively [39, 40].

Self-efficacy can be modified over time and through interventions aimed at alleviating symptoms associated with cancer therapy [10, 41, 42]. Peer support has been shown to have a positive impact on the self-efficacy of (AYA) cancer patients, as demonstrated in several studies [43–47].

The overall body of data from evidence-based peer support interventions for AYAs is very limited. The majority of studies have examined the effects of peer support in AYAs in group settings (e.g., professionally facilitated group intervention or internet-based groups), app-based or with healthy peers, and on psychosocial outcomes such as coping, quality of life, cancer-specific knowledge, social support or health-promoting behaviors [48]. Further research is needed on how to design peer-to-peer support programs as part of non-professional psychosocial support to provide the best care for young adult cancer with a particular focus on enhancing self-efficacy to improve coping behaviors.

## Methods

### Aim

The aim of the following study is to investigate how effective a mentoring program (Peer2Me) can be in increasing the self-efficacy of young cancer patients (mentees) in the short and medium term.Hypothesis I: Participation in Peer2Me will lead to a significant increase in self-efficacy compared to the control group receiving standard psycho-oncological care. This effect will remain stable for at least 3 months.

In addition, the study aims to demonstrate whether Peer2Me is effective in reducing psychological distress and improving health literacy and social support.Hypothesis II: Participation in Peer2Me will lead to a significant reduction in psychological distress compared to the control group receiving standard psycho-oncological care. These effects will remain stable for at least three months.Hypothesis III: Participation in Peer2Me will lead to a significant improvement of health literacy compared to the control. This effect will remain stable for at least 3 months.Hypothesis IV: Participation in Peer2Me will lead to a significant improvement of social support compared to the control. This effect will remain stable for at least 3 months.

Furthermore, we assume that the mentoring program can improve the mentors’ empathy skills and post-traumatic growth as well as their life satisfaction.

### Study design

The study is designed as a bi-center (university medical centers in Leipzig and Hamburg) comprehensive cohort study (CCD) [49] with a 1:1 allocation ratio over a period of 36 months and assessments at baseline and 3 and 6 months after the intervention. In this study design, eligible participants can choose to be randomized. In addition, patients who are not interested in participating in the Peer2Me intervention or the control group will be asked to complete the accompanying questionnaires at the three measurement time points. This will provide an additional no-intervention comparison group that will be relevant for comparison, in particular if the willingness to randomize in the study sample turns out to be very low.

### Recruitment

Acute AYA cancer patients (mentees) and mentors are recruited from January 2021 to June 2024 in the cooperating clinics (Hamburg and Leipzig in Germany) through personal approach by the study team. Eligible patients are invited to participate in a face-to-face meeting or by mail, and the invitations are followed up by telephone or e-mail. In addition, there is an ongoing successful cooperation with the psycho-oncological counselling services of the various cancer centers in Leipzig and Hamburg. Information about the study is also provided via study flyers and announcements as well as via social media postings (Facebook, Instagram), so that self-registration is also possible.

### Intervention

Peer2Me is a 1:1 mentoring program that aims to support acutely ill young adults with cancer with the help of a mentor in their immediate coping with the disease, thereby increasing their experience of self-efficacy and reducing their psychological distress. Between 2019 and 2020, a pilot study was conducted to evaluate the feasibility and utilization of this mentoring project [50].

The mentor’s support is intended to meet the need for emotional or psychosocial support. She or he assumes the role of a communication partner using her or his experience to help the mentee cope with the disease and the course of treatment.

Once mentors have been recruited, and if the results of the SCID and the initial interview are successful, they will attend mentor training. Participation in this training, which includes self-awareness components, is mandatory for mentors. The two-day training (6 h per day) takes place in a face-to-face or online setting in Hamburg or Leipzig with 10 to 12 participants and is conducted by psycho-oncologically experienced study staff. The content of the training includes basic client-centered communication skills and elements of motivational interviewing [51, 52]. This is intended to introduce the mentors to appropriate interview techniques such as active listening, open-ended questions, etc. In addition, the mentors are given the opportunity to learn about and reflect upon their role as a “former patient” and as a mentor. In this context, the boundaries of the mentors play an essential role. It is important that the mentors are protected in their role, are not pressured to act as medical experts or psychotherapists and are not expected to be able to answer expert questions. They should also be able to distance themselves from potentially excessive or inappropriate expectations of mentees. Other components include the acquisition of skills and exercises to improve disease management. In addition, mentors are provided with general medical (common tumor entities, long-term sequelae) and basic psychosocial knowledge about cancer in young adulthood and existing support services for the AYA patient group, such as support groups or cancer counseling centers. Both mentors and mentees also receive a folder with information (brochures, flyers, guides), and the latter will be able to contact their mentor, if they have any questions.

The intervention begins by matching the tandems (mentor and mentee) by age, diagnosis, and gender, if possible. At the first meeting of each tandem, a study staff member will be present to explain the Peer2Me study process and agenda, distribute cancer-specific and psychosocial information materials, and to conduct the baseline assessment (t1). Participants are either provided with a link to complete the standardized study questionnaire online using Lime Survey, or, if preferred, a printed version of the questionnaire is sent.

The tandem itself will then determine the frequency, duration, and type (face-to-face or telephone) of subsequent contacts between mentor and mentee over the following three months. However, at minimum of 4 documented contacts should take place for the purposes of the evaluation (fewer than 4 contacts are considered as a termination of intervention). The mentor documents each interaction, including the key issues discussed with the mentee, and informs the study team. After 3 months, a formal final meeting of the tandem will be held together with a member of the study team, during which the assessment t2 is conducted. The final survey (t3) will be sent to all mentees 3 months after the intervention.

Group supervision for the mentors will take place once a month. It will be provided by a psychologist with appropriate psycho-oncological and group therapy expertise.

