### Control group

Study participants in the control group will receive a one-time standardized 30-minute psycho-oncological consultation, including appropriate information material, as part of the AYA consultation at their study center. The t1 survey will also take place during this consultation. The t2 and t3 surveys will be conducted via e-mail or mail with appropriate invitations and reminders. A detailed study flow is shown in Fig. 2.

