### Randomization

The Comprehensive Cohort Design (CCD), or Patient Preference Trial, is an alternative to a randomized controlled trial. It is used when patient preference needs to be taken into account or when it is hypothesized that there is a relatively high preference for participation in a particular intervention [49, 54]. In the CCD, potential study participants are asked at the start of the trial if they agree to be randomized. If they agree, randomization takes place. If they refuse randomization, they can choose which study arm they will be assigned to. The CCD offers several advantages that are crucial for the successful implementation of this psycho-oncological intervention study, such as the possibility to include all potential study participants (including patients who refuse randomization) and a lower drop-out-rate in the control arm. If randomization is sufficient, an analysis similar to the RCT study is possible.

A limitation of the CCD is the difficulty in predicting the willingness of participants to be randomized. It is not possible to make clear statements about this in advance, especially as the present mentoring project is the first peer-supported intervention for young adult cancer patients in Germany.

If a sufficient number of study participants have been randomized in each study arm, analyses will be performed within the randomized arms and the non-randomized participants will be used to check external validity. If insufficient participants agree to randomization, all data will be analyzed as a prospective cohort study.

Potential study participants are fully informed about the study, the different study arms, and the main data to be collected. As a next step is to check the inclusion criteria and determine whether randomization can take place or whether there is a clear patient preference.

Randomization of study participants is performed within three working days by an independent documentation assistant of the Leipzig study center using the randomization software RITA. Block randomization with variable block length will be used to achieve a better balance. Stratification by gender and age will be performed for each study center to ensure structural equality for the intervention and control groups.

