### Statistical analysis

#### Power and sample calculation

The number of cases was planned with the GPower program using a significance level of α = 0.05 and a power of (1-ß) = 0.8070. The primary outcome measure self-efficacy is used to demonstrate the effectiveness of the intervention. We make the following assumptions about changes in the intervention and control group: The pre-post effect size used is the effect size for self-efficacy.

d = 0.43, which could be found in the literature [68]. The expected controlled effect size requires a minimum of 90 subjects per group (180 subjects in total) measured with the U-test for independent groups. For this group size (*N* = 180), an analysis of variance with repeated measures (two groups, three measurements, correlation between measurements *r* = 0.5, epsilon = 1) can already demonstrate the following small effects: for comparisons between factors (IG vs. CG): f > 0.17; comparisons within factors (across measurement time points): f > 0. 09; and interaction effects between the two groups and time: f > 0.09. The sample thus has sufficient power to detect at least medium effects between the groups, as well as small effects within the groups and small interaction effects between the groups considering the measurement time points.

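### Only the intervention arm's start, t1 and t2 depend on finding a mentor after allocation, which risks arm-specific delay and loss of unknown size

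*Protocol article*

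**What the plan says.** All references are to the protocol article.

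- **Before allocation (Randomization).** Patients are informed, the inclusion criteria are checked, and it is established whether the patient accepts randomisation or has a clear preference. Then: "Randomization of study participants is performed within three working days by an independent documentation assistant". Having a mentor at hand is not named as a condition.
- **After allocation, intervention arm (Intervention).** "The intervention begins by matching the tandems (mentor and mentee) by age, diagnosis, and gender, if possible". A staff member attends the first tandem meeting and conducts t1 there; t2 is conducted at the closing tandem meeting three months later. Questionnaires are completed through an online link or on paper. t3 goes to all mentees three months after the intervention.
- **Mentors (Abstract, Intervention and Eligibility criteria).** The abstract puts training before matching: "Following mentor training, mentees and mentors are matched by diagnosis, age, and gender". Mentors must pass a structured clinical interview and attend a two-day course, face-to-face or online, "in Hamburg or Leipzig with 10 to 12 participants".
- **After allocation, control arm (Control group).** Controls "will receive a one-time standardized 30-minute psycho-oncological consultation". Their t1 is taken at that consultation, and t2 and t3 go out by e-mail or mail.
- **Analysis (Abstract).** Intention to treat, comparing patients by assigned group.

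**The concern.** Randomisation makes the arms comparable at allocation. Here one arm must then pass a further step, finding a mentor, before its baseline can be taken, and the other arm has no such step. Two consequences follow.

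1. **Delay.** Entry requires a diagnosis within the previous 6 months, and the target is the acute phase. A wait for a mentor moves mentees' assessments to a later point after diagnosis than those of controls.
2. **Loss.** A mentee who never forms a tandem has neither of the meetings at which t1 and t2 are taken. Unless handled otherwise, that patient leaves the intervention arm without data. Any such loss could be related to diagnosis, age and gender, the variables used for matching.

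At stake is whether the comparison by assigned group can be carried out on everyone who was assigned.

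**Working it through.** **Step 1. Order of events.** Setting the sections side by side:

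| | Intervention arm | Control arm |
|---|---|---|
| Checks before allocation | inclusion criteria, preference | the same |
| Needed before t1 | a trained mentor and a first tandem meeting | a consultation appointment |
| Occasion of t2 | closing tandem meeting | e-mail or mail invitation |
| Allocated treatment not started | no scheduled t1 or t2 | no scheduled t1; t2 does not depend on a meeting |

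No single sentence says that a mentor is looked for only after allocation. It follows from matching being the first step of the intervention and from the two checks named before randomisation.

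**Step 2. Reproduce the planned sample size.** Inputs from Power and sample calculation: "using a significance level of α = 0.05"; "a power of (1-ß) = 0.8070" (possibly 0.80 with a reference number fused to it in the text extraction); "d = 0.43, which could be found in the literature"; U-test; 90 per group. The power of the U-test is approximated by a two-sided two-sample t-test with each group size multiplied by 3/π, its asymptotic relative efficiency under normality.

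- Effective size per arm: 90 × 3/π = 85.94
- Noncentrality: 0.43 × √(85.94/2) = 2.82, with 2 × 85.94 − 2 = 169.9 degrees of freedom
- Power: 0.8003

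So 90 per group is reproduced at 0.80 (92 at 0.807). The sample has no reserve for non-receipt or loss.

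**Step 3. Illustrate an unmatched share u.** The article gives no value, so 5%, 10% and 20% are assumptions (4.5, 9 and 18 of 90 mentees). For any one unmatched patient, two alternatives exist:

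- (a) Kept and analysed as allocated, with no effect: the effect becomes 0.43 × (1 − u), with 90 per arm.
- (b) Lost: the effect stays at 0.43, and the intervention arm shrinks to 90 × (1 − u).

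| u | (a) effect | (a) power | (a) per arm for 0.80 | (b) mentees left | (b) power |
|---|---|---|---|---|---|
| 0 | 0.430 | 0.80 | 90 | 90 | 0.80 |
| 5% | 0.409 | 0.76 | 100 | 85.5 | 0.79 |
| 10% | 0.387 | 0.71 | 111 | 81 | 0.78 |
| 20% | 0.344 | 0.61 | 140 | 72 | 0.75 |

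**Step 4. Selection bias under (b).** The bias in the intervention mean would be u times the outcome difference between retained and lost mentees. The article gives neither term, nor the sign of the difference, so no figure is offered.

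**Step 5. Delay.** A late match moves t1 and t2 together, so the three months between them are kept. What differs between arms is time since randomisation and since diagnosis. No waiting time is given.

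**The case against.** A reader might infer that intervention patients with rare tumours, or those enrolled between courses, do wait or never start, so that the arm is delayed, diluted and selectively depleted. The documents do not support that.

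- Matching on age, diagnosis and gender applies only where possible, so a poor match need not block a start.
- Mentors are trained before matching and recruited throughout the study, and courses may be held online. Nothing documents a shortage, a limit of one mentee per mentor, or displacement of randomised mentees by those who chose Peer2Me.
- A pilot examined feasibility and utilisation; its results are not shown here.
- Dilution and depletion are alternatives for the same patient, and dilution under intention to treat is a legitimate estimate of the programme as delivered.
- Controls can also miss their consultation or later surveys; only mentor-related loss is confined to one arm.
- Missing values are to be imputed. Age and gender are known for everyone as stratification factors, and eligibility is checked against patient records.

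These objections remove any claim about how often the problem occurs. It can also be said that the maximum wait and the handling of an unmatched mentee belong in the full protocol, and their absence from an article is not held against it. What remains is what the article does state: t1 and t2 are fixed to tandem meetings in one arm only. The link and paper form show that another route exists, but the stated occasion for both assessments is still the meeting. Imputation can use the known covariates, but for a mentee without t1 and t2 it would have to supply both the baseline and the first outcome.

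**Conclusion.** The concern holds as a structural risk, not as a demonstrated loss. Treatment start, t1 and t2 depend on a mentor found after allocation in the intervention arm, with no counterpart among controls. This exposes the comparison by assigned group to arm-specific delay and missing data.

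Its size is unknown. The power figures (0.76, 0.71 and 0.61 if unmatched mentees are kept; 0.79, 0.78 and 0.75 if they are lost) rest on assumed shares of 5%, 10% and 20%, no effect without a mentor, the plan's d = 0.43 and the U-test approximation. The planned hypothesis tests are repeated-measures analyses of covariance, so these figures describe the sample-size calculation rather than the final model. Loss costs little power; its danger is selection bias, which the documents give no basis to quantify.

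**What to change.** 1. Detach t1 and t2 from the tandem meetings. Send both to every randomised patient by the existing link or post channels, on the same schedule in both arms. For patients already past t1, apply this to whatever is still outstanding.
2. Keep unmatched mentees in the randomised comparison as allocated.
3. Report by arm the days from randomisation to first session (tandem meeting or consultation) and the number who never had one, including the number of mentees never matched.

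The channels already exist, so the cost is some mailing and follow-up. One consequence should be accepted openly: for a mentee matched late, t2 may fall before three months of mentoring are complete. That belongs to the effect of being assigned to the programme.

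By the stated dates recruitment ran to June 2024. If any enrolment continues, also confirm that a trained mentor is available before sending the randomisation request. The downside is slightly slower accrual, and patients who are hard to match may wait before entry, so the check should not become a reason to exclude them.

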**Fig. 2 Fig2:**
[figure not shown]
Study flow

In the allocation or preference for the control condition, study participants receive a one-time standardized 30-minute counseling session with relevant information material in the AYA clinic at their study center. The t1 assessment also takes place during this AYA clinic counseling session. The t2 and t3 assessments will be conducted online or via postal mail with appropriate invitations or reminders.

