#### Statistical methods

Quantitative data will be analyzed using the statistical program SPSS 29.0 [69]. First, the items of the scales of the primary and secondary outcomes are checked for missing values. Items and complete sociodemographic variables that violate the MCAR (missing completely at random) assumption are identified in each subanalysis using Little’s MCARTest. Missing values are then estimated using the Markov Chain Monte Carlo (MCMC) procedure. This procedure yields reliable results even with high proportions of missing values for both the MCAR and MAR (missing at random) missing value patterns. On the other hand, it is suitable for any patterns of missing values, but also for monotonic patterns.

Descriptive analyses are calculated for all variables and presented as frequencies, means, standard deviations and ranges. Sociodemographic and medical predictors of intervention effectiveness are identified using stepwise backward regression. Non-dichotomous categorical characteristics are first subjected to multifactorial analysis of variance. Games-Howell correction or Bonferroni-Holm correction is used as a post hoc test, as appropriate. Correlation analysis is performed prior to each regression to avoid multicollinearity. Mean comparisons using one-way factor repeated measures analyses of covariance (ANCOVA) are used to test the hypotheses.

The first step is to compare only the randomized groups. In the next step, the preference groups are analyzed to determine differences in the effects compared to the randomization groups. Finally, all four groups are compared with each other, adding an indicator variable (randomization/preference) as a covariate. If the number of randomized study participants is too small, the data must be analyzed as a prospective cohort study.

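### The t1 baseline is taken after allocation and inside each arm's first session, so comparisons that use it are at risk of bias

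*Protocol article*

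**What the plan says.** The abstract's Methods paragraph states: "Outcomes will be measured at baseline before the intervention (t1"). The body of the article places t1 elsewhere.

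- **Intervention arm** (Intervention section). The start of treatment is defined: "The intervention begins by matching the tandems (mentor and mentee) by age, diagnosis, and gender, if possible". At the tandem's first meeting, a staff member is there to explain the programme, "distribute cancer-specific and psychosocial information materials, and to conduct the baseline assessment (t1"). The questionnaire is offered as an online link or, "if preferred, a printed version of the questionnaire is sent".
- **Control arm** (Control group section). The treatment is one 30-minute consultation, and "The t1 survey will also take place during this consultation". The text under Fig. 2 repeats this for participants allocated to, or preferring, the control condition: "The t1 assessment also takes place during this AYA clinic counseling session".
- **Randomization section.** It describes information, the eligibility check and then allocation: "Randomization of study participants is performed within three working days by an independent documentation assistant". No outcome assessment is placed before allocation.
- **Table 1.** It has a t0 screening column for the intervention and control groups, but GSE, CBI-B, GAD-7, PHQ-9 and the other outcome scales for these groups start at t1.
- **Statistical methods.** "Mean comparisons using one-way factor repeated measures analyses of covariance (ANCOVA) are used to test the hypotheses". The section does not say whether t1 is a covariate or one of the repeated measures.

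**The concern.** A baseline is safe to adjust for, or to subtract, because allocation cannot have affected it. Here a patient answering t1 already knows the arm and may have met the mentor or begun the consultation. The outcomes are self-reported, and self-efficacy, the primary outcome, is what mentoring is meant to raise. The two first sessions also differ in kind: one introduces a matched survivor, the other is a professional consultation.

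If those circumstances move t1 by different amounts in the two arms, the analysis treats the difference as chance imbalance and removes some or all of it from the effect estimate. A positive net shift (intervention minus control) hides benefit. A negative one creates apparent benefit. Hypothesis I is at stake, and so are the secondary hypotheses tested in the same way.

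**Working it through.** **Inputs from the Power and sample calculation section:** d = 0.43, 90 per group (N = 180), α = 0.05, three measurements, r = 0.5, epsilon = 1. Sidedness is not stated.

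**The plan's own figure first.** A two-sided t-test with d = 0.43 and 80% power needs 86 per group. Dividing by the U-test's asymptotic relative efficiency, 3/π, gives 86/0.955 = 90.06, which agrees with the stated 90. A one-sided test would need only about 67 before that correction, so two-sided is assumed. The detectable effects also reproduce: f = 0.171 between groups, and 0.095 within groups and for the interaction. No stated figure is wrong.

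**When t1 falls.** A tandem exists only after assignment and matching, and a control consultation only for someone assigned to or choosing control. t1 is therefore post-allocation in both arms. In the intervention arm it also follows matching, which the article names as the start of the intervention. Whether it follows any session content is left open.

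**Effect of a shift.** Let s be the net t1 shift (intervention minus control, in SD units) caused by allocation or the first session. The documents give no value, so s is an assumption.

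- Change from t1 estimates d − s.
- ANCOVA with t1 as covariate estimates d − r·s = 0.43 − 0.5s, with SE = √((1 − 0.25) × 2/90) = 0.129. A simulation of 4,000 trials at s = 0.2 gave 0.326, against 0.33 from the formula.
- For the three-wave group-by-time test, the group differences are (s, 0.43, 0.43). Then f² = (0.43 − s)²/18 and λ = N·m·f²/(1 − r) = 1080f² = 60(0.43 − s)², on 2 and 356 degrees of freedom. At s = 0, λ = 60 × 0.1849 = 11.09. At s = 0.2, λ = 60 × 0.0529 = 3.17.

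| Assumed s | Change estimate | ANCOVA estimate | ANCOVA power | Interaction λ | Interaction power |
|---|---|---|---|---|---|
| −0.1 | 0.53 | 0.48 | 96% | 16.85 | 96% |
| 0 | 0.43 | 0.43 | 91% | 11.09 | 85% |
| 0.1 | 0.33 | 0.38 | 83% | 6.53 | 62% |
| 0.2 | 0.23 | 0.33 | 72% | 3.17 | 34% |

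**No true effect at t2.** A shift of |s| = 0.1 raises the two-sided rejection rate from 5% to 10% (change score) or 7% (ANCOVA). With |s| = 0.2 it is 27% or 12%.

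**Without t1.** A comparison of t2 values alone estimates 0.43 for every s, with SE = √(2/90) = 0.149 and power of about 82%.

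**The case against.** A reader might infer that t1 is a post-treatment measure and that every comparison referring to baseline is biased. The documents do not support that.

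- The Intervention section lists the staff member's tasks without fixing their order, and the control text says only that t1 happens during the session. The questionnaire could be filled in first, which would make it post-allocation but pre-exposure. Fig. 2 is not available to settle this. The link or mailed form also means that completion in the mentor's presence is not stated.
- Between-arm bias needs unequal shifts. Equal shifts cancel between arms, although within-arm change would still be distorted. Nothing in the documents gives a non-zero s or its sign, and GSE is described as a general sense of self-efficacy, which one meeting may not move.
- t1 as covariate is not stated. The only covariate that the article names is the randomization/preference indicator.
- A reader might also infer that losses between allocation and t1 are arm-specific and undermine the intention-to-treat comparison. No loss rates are given, controls also wait for an appointment, and imputation is planned. This remains conjecture.
- Recruitment was to end in June 2024 and the article appeared on 2 July 2024, so moving t1 may help few or no patients.

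All of this stands as a limit on strength. It does not remove the contradiction with the abstract or the absence of any outcome measurement protected from allocation. In a repeated measures ANCOVA, t1 would ordinarily enter as an outcome wave or as a covariate, and either use is exposed.

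**Conclusion.** The point holds in limited form. As written, t1 is certainly post-allocation (or post-preference), possibly post-exposure, and inconsistent with the abstract. Change, group-by-time and t1-adjusted comparisons are at risk of bias whenever the arms shift differently at t1: by −s for the first two and −0.5s for ANCOVA.

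The range of s from −0.1 to 0.2 SD is illustrative. It rests on the plan's d, r and sample size, a two-sided test, a true effect of 0.43 at both t2 and t3, and complete data. At s = 0 there is no between-arm bias. Comparisons of t2 or t3 values that do not use t1 are unaffected, including the U-test behind the sample size if it is applied to those values. The planned 90 per group needs no change.

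**What to change.** 1. Reconcile the abstract with the Intervention section, the Control group section and the text under Fig. 2. State when t1 was completed relative to allocation and to session content.
2. For any participant still to be enrolled, have the existing online or paper t1 questionnaire completed after consent and before allocation is released.
3. For participants already measured, prespecify between-arm analyses of t2 and t3 that do not use t1, adjusted for the randomization stratifiers (gender, age, centre), and report the timing of t1 as a limitation. Given the recruitment dates, this may be the main part still usable.

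**Cost.** No extra visits or patients are needed. A few patients may complete t1 and then not start. Analyses without t1 lose some precision: at r = 0.5 the SE rises from 0.129 to 0.149, and power at t2 falls from about 91% to about 82% (before any gain from the stratifiers), which is still above the planned 80%.
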